**Fig. 2 Fig2:**
[figure not shown]
Schedule of enrolment, interventions, and assessments. SPIRIT 2013 recommended content for the schedule of enrolment, interventions, and assessments

### Sample size

The sample size was calculated based on the CCA blood flow results reported previously [11]. With an expected difference of 10 cm/s in peak systolic velocity of the CCA between group means, an SD of 10 cm/s, α = 0.05, and β = 0.8, a sample size of 17 patients was required in each group. To compensate for a dropout rate of up to 10%, we will enrol a total of 38 cases (19 for each group) for this study. Although the study is powered to allow a 15% dropout rate, we will make every effort to minimise patient loss and missing data during the trial period.

### Randomisation

Participants will be randomly allocated to either group 1 or group 2 with a 1:1 allocation defined by a computer-generated randomisation using the R package (R Foundation for Statistical Computing). The random allocation sequence will be generated by a statistical expert. Randomisation will be under the control of a single investigator who will be the only person allowed to manage the electronically secured file containing the subject randomisation assignments. This investigator will be blinded to the group to which the participants are allocated.

### Blinding

The participants, researchers, and outcome assessors will remain blind to group allocation throughout the study. Participants will be assigned codes and will be concealed during the allocation process to ensure proper blinding. The researchers responsible for performing the intervention and evaluating the outcomes will not know the study design, allocation, objectives, or expected outcomes.

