**Methods:**

A randomized controlled crossover trial with 38 participants will be conducted. Participants who have primary headaches will be assigned to either group A or B. Patients in group A will receive SGB with 6 ml 1% lidocaine, and after a one-week washout period, they will undergo the second SGB with 6 ml normal saline. In contrast, patients in group B will receive the opposite protocol. Data will be collected at baseline (T0) and at 15 min after the first intervention (T1), 15 min before the second intervention (T2), 15 min after the second intervention (T3) and at a 3-week follow up (T4). T1 is the primary time point for the primary outcome analysis. The primary outcomes include the peak systolic velocity (PSV), the end diastolic velocity (EDV), resistance index (RI) and vessel diameter of the common carotid artery (CCA) and vertebral artery (VA). The secondary outcomes include the rate of ptosis, the rate of conjunctival flushing, and the numerical rating scale (NRS) pain score. Additionally, adverse events (AEs) or serious adverse events (SAEs) will be collected at each assessment point.

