### Intervention

All participants will undergo two SGBs, with a one-week washout period between them. For the ultrasound-guided SGB, each patient will receive 6 mL 1% lidocaine and 6 mL normal saline at one-week intervals to allow a washout period for the injection. The 1% lidocaine is composed of 2% lidocaine and normal saline in a 1:1 ratio (for example, the 1% lidocaine 2 mL is prepared by combining 2% lidocaine 1 mL, and normal saline 1 mL) [18, 19].

The patients will be positioned in a supine position with their neck slightly hyperextended. Prior to the procedure, the C7 level is confirmed by the use of a 7–14 MHz linear probe (S-Nerve, Sonosite, USA). On the short-axis view, the posterior tubercle and the vertebral body show as a slope in the transverse process of C7. Sonoanatomy of the neck at the C7 level is confirmed by the absence of the anterior tubercle. The thyroid, inferior thyroid artery, oesophagus, internal jugular vein, CCA, VA, and prevertebral fascia are also confirmed. Colour Doppler imaging is utilised to avoid penetrating the CCA, VA, and the internal jugular vein during the needle insertion. The neck area will be sterilised and the probe will be covered with sterilised vinyl. At the C7 level, the probe will be placed at the anterior scalene muscle, which is located between the carotid sheath and the brachial plexus. A 25-gauge, 6-cm needle will be inserted laterally, 5 mm from the probe. The needle tip is placed posterior to the carotid artery and anterior to the longus colli muscle under the transverse short axis for the in-plane approach. The assigned dosage of 1% lidocaine or normal saline will be injected in the patients.

At the end of the SGB, another doctor, who is not involved in the operation, will observe the ptosis and conjunctival flushing. Before and 15 min after the SGB, the flow measurements will be recorded by an ultrasound specialist. Sonograms will be obtained with a Mylab 90 (Genova, Italy) by using a linear probe (curved-array transducer, CA431, 1–8 MHz).

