#### Secondary outcomes

Secondary outcomes include: (1) the PSV, EDV, RI, and diameter of the CCA and VA at T0, T2, T3, and T4; (2) the rate of ptosis and conjunctival flushing at T1 and T3 (ptosis and conjunctival flushing are considered the standard indicators of SGB of success [25]); (3) the numerical rating scale (NRS) at T0 and T4. The NRS allows the patient to describe the intensity of his/her pain as a number, usually ranging from 0 to 10, where 0 means no pain and 10 means pain as “bad as it could be” [26].

Adverse events (AEs) or serious adverse events (SAEs) will be collected at each assessment time point and any AEs or SAEs related to the intervention will be reported. For an overview of the schedule of enrolment, interventions, and assessments please see Fig. 2.

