### Data collection process

We will confirm eligibility criteria are met through review of the participant’s medical records. The following data will be collected for each participant: patient identifiers and demographic information, study intervention details, and the peak systolic velocity, vessel diameter, and RI of the CCA and VA, as measured at T0, T1, T2, T3, and T4. The rate of ptosis and conjunctival flushing will be measured at T1 and T3; the pain scores will also be recorded at T0 and T4.

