### Monitoring of data quality

The peak systolic velocity, vessel diameter, and RI of the CCA and VA will be detected by an ultrasound specialist using the same ultrasound instrument. The rate of ptosis and conjunctival flushing will be recorded by a doctor. Another pain physician will teach patients to use the NRS scoring system and then record pain scores. Data are directly recorded in the electronic study database, which is backed up regularly. All of the assessors will be blinded from the information linking participants and interventions. Study participation will last 3 weeks from enrolment for each participant. No interim analysis will be performed during the study.

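### Blinding of participants and all outcome assessors is claimed for the whole study, but the signs of a working block can be seen when the primary neck scan is made

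*Protocol article*

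**What the plan says.** The Blinding section makes an unqualified claim: "The participants, researchers, and outcome assessors will remain blind to group allocation throughout the study". It adds that "The researchers responsible for performing the intervention and evaluating the outcomes will not know the study design, allocation, objectives, or expected outcomes". Monitoring of data quality repeats the claim for assessors in narrower terms: "All of the assessors will be blinded from the information linking participants and interventions".

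Under Secondary outcomes, "ptosis and conjunctival flushing are considered the standard indicators of SGB of success". Data collection process fixes when they are recorded: "The rate of ptosis and conjunctival flushing will be measured at T1 and T3". On the scan, the Intervention section says: "Before and 15 min after the SGB, the flow measurements will be recorded by an ultrasound specialist". The Abstract states that "T1 is the primary time point for the primary outcome analysis", and Primary outcomes places T1 at 15 minutes after the first block.

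Some separation of roles is planned. The Intervention section gives the sign scoring to a doctor who does not perform the block. Monitoring of data quality gives the scan to an ultrasound specialist, the signs to a doctor and the pain scores to another physician.

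On allocation, the Randomisation section gives one investigator sole management of the file of assignments and then says: "This investigator will be blinded to the group to which the participants are allocated".

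**The concern.** The comparison is lidocaine against saline, and the protocol itself treats two visible facial signs as evidence that the block has worked. A sonographer examining the neck 15 minutes after injection may see them. Withholding the list that links participants to injections does not withhold a drooping lid or a red eye.

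The primary outcomes are readings taken by that specialist. If a belief about the treatment affects how the scan is made or read, the T1 comparison carries a systematic component that randomisation does not remove and a larger sample does not reduce. A reader of the results would also rely on a statement of full blinding that the described procedures cannot guarantee.

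**Working it through.** **Setting the passages side by side**

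| Step | Source in the protocol article | Content |
|---|---|---|
| 1 | Trial design | Each period gives 6 ml of 1% lidocaine or 6 ml of saline |
| 2 | Secondary outcomes | Ptosis and conjunctival flushing mark a successful block |
| 3 | Data collection process | Signs recorded at T1 and T3 |
| 4 | Primary outcomes; Intervention | Primary scan by the ultrasound specialist at T1, 15 minutes after the block |
| 5 | Blinding | Participants, researchers and assessors blind for the whole study |

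Steps 1 to 4 mean that, where a block shows signs, a visible marker of lidocaine is present when the primary measurement is due. Step 5 can then hold for the sonographer only if something keeps the signs from view. The measures described are participant codes, separate staff, and ignorance of the design and expected results. None does that. For the doctor who scores the signs, looking at them is the task.

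One timing detail is loose. The Intervention section places the sign observation at the end of the block, while Secondary outcomes and Data collection process place it at T1. On either reading the signs are looked for in the interval that leads up to the T1 scan.

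**Reproducing the plan's own figure**

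Inputs from Sample size: difference 10 cm/s, SD 10 cm/s, α = 0.05 (two-sided assumed), and the stated β = 0.8 read as power 0.8.

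- Normal approximation: n = 2 × (1.96 + 0.84)² × 10²/10² = 15.7, so 16 per group.
- Two-sample t-test: 16.71, so 17 per group, with power 80.7%.
- Dropout: 17/0.9 = 18.9, so 19 per group and 38 in total.

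The stated 17 and 38 reproduce. They give a scale for judging a bias.

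**What a bias would do at T1**

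The documents give no size for observer bias, so the shift b is an assumption, taken from 1 to 5 cm/s (10% to 50% of the planned difference), with no true effect.

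- SE = 10 × √(2/17) = 3.43 cm/s.
- False-positive rate = probability that a noncentral t with 32 degrees of freedom and noncentrality b/SE falls outside the two-sided 5% limits.

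| b (cm/s) | b/SE, 17 per group | Rate, 17 per group | Rate, 19 per group |
|---|---|---|---|
| 1 | 0.29 | 5.9% | 6.0% |
| 2 | 0.58 | 8.7% | 9.2% |
| 3 | 0.87 | 13.6% | 14.7% |
| 4 | 1.17 | 20.5% | 22.4% |
| 5 | 1.46 | 29.3% | 32.3% |

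Here b is the average shift over all lidocaine patients. If only a fraction p of blocks show signs that are noticed and acted on, the average is p × b. For example, 4 cm/s in half the patients averages 0.5 × 4 = 2 cm/s, or about 8.7% at 17 per group, ignoring the small added spread.

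**The case against.** The strongest reply is that the plan already has real safeguards. Different people inject, score the signs, scan and record pain. Assessors are denied the allocation link and are said not to know the expected results. The article is condensed, and it does not describe the patient's position during the scan or where the sonographer looks. Draping may be among the details left to the full protocol. This lowers the risk and makes unmasking possible or likely rather than certain. It does not rescue an unqualified claim that the article itself makes, and that claim cannot hold for the doctor who scores the signs.

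Three stronger readings are tempting, and the documents do not support them.

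- **That bias would always run one way.** The Background reports conflicting earlier findings on carotid and vertebral flow, and the Blinding section says assessors do not know the expected outcomes. A systematic shift is possible, but its direction is not given.
- **That the crossover makes matters much worse for the primary result.** A contrast between visits can help guessing only at T3, which is secondary. At T1 there has been one injection. Applying a 3 to 5 cm/s shift to a crossover test (SE = 10/√34 = 1.71, assuming a correlation of 0.5) gives about 42% to 83%, but that is not the T1 comparison.
- **That the investigator who manages the allocation file cannot be blinded.** The Randomisation section speaks of groups 1 and 2, and the Blinding section mentions participant codes. A file of coded labels could be managed without knowing which label means which sequence. The wording needs clarifying, but it is not a proven contradiction.

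**Conclusion.** The point stands in a limited form. The protocol promises blinding of participants and every outcome assessor for the whole study, and the procedures it describes do not secure this for the ultrasound specialist at T1 or T3, or for the doctor scoring the signs. This is a threat to the primary measurements and not evidence that they are biased.

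Its size is unknown. Over an assumed shift of 1 to 5 cm/s at T1, the nominal 5% error rate becomes about 6% to 29% with 17 per group. The low end is negligible, the high end is serious, and partial unmasking moves the result towards the low end. The range rests on no true effect, SD 10 cm/s, a two-sided t-test, and the premise that a belief about treatment can move the reading.

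**What to change.** - For every remaining scan after an injection (T1 and T3), cover the patient's eyes and upper face before the ultrasound specialist enters. Covering at the other scans too would keep the procedure uniform.
- Sign scoring by a separate doctor is already planned. Add that the scores are not disclosed to the specialist.
- After each such scan, record the specialist's and the patient's guess at the treatment, and report the guesses.
- Reword the Blinding section so that it claims blinding only for roles that can be kept blind, and leaves out the doctor who scores the signs. Bring it into line with Setting, which calls the trial investigator- and observer-blinded without naming participants.
- In the Randomisation section, state whether the file holds only coded labels and who holds the key.
- Report which scans were made without shielding.

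The cost is a drape and one question per visit, with a few corrected sentences. No treatment or extra staffing is involved. The limit is coverage. Trial status gives 27 of 38 enrolled by 12 October 2017, leaving 38 − 27 = 11 participants still to enter, plus any scans still due for those already enrolled. If scanning has finished, the wording can still be corrected and the limitation reported.

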### Data collection process

We will confirm eligibility criteria are met through review of the participant’s medical records. The following data will be collected for each participant: patient identifiers and demographic information, study intervention details, and the peak systolic velocity, vessel diameter, and RI of the CCA and VA, as measured at T0, T1, T2, T3, and T4. The rate of ptosis and conjunctival flushing will be measured at T1 and T3; the pain scores will also be recorded at T0 and T4.

### Monitoring of data quality

The peak systolic velocity, vessel diameter, and RI of the CCA and VA will be detected by an ultrasound specialist using the same ultrasound instrument. The rate of ptosis and conjunctival flushing will be recorded by a doctor. Another pain physician will teach patients to use the NRS scoring system and then record pain scores. Data are directly recorded in the electronic study database, which is backed up regularly. All of the assessors will be blinded from the information linking participants and interventions. Study participation will last 3 weeks from enrolment for each participant. No interim analysis will be performed during the study.

### Statistical analyses

Baseline demographic characteristics, including individual variables such as age, sex, weight, and other baseline values, will be expressed with descriptive statistics for the two groups. We will use the SPSS Statistics V. 21.0 (SPSS-IBM®) to perform all statistical analyses. The normality and homogeneity of all variable distributions will be tested with the Shapiro-Wilk test and Levene’s test, respectively. For nonparametric data, the Friedman test will be used followed by the Wilcoxon post hoc test. We will use two-way (2 × 4) ANOVA for inferential statistical analysis of the parametric data, with Tukey’s post hoc tests. All data will be represented by the mean ± standard deviation. Significance level will be set as α ≤ 0.05.

The main analysis will be performed after all patients have completed the study. A statistical analysis plan will be written before the data are analysed.

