### Trial design

A double-blinded, randomized controlled crossover trial will be conducted, and all subjects will undergo ultrasound-guided SBG. Group A will first undergo SGB with 6 ml 1% lidocaine. After a one-week washout period, this group will receive ultrasound-guided SGB with 6 ml normal saline. In contrast, group B will receive the opposite protocol. That is, group B subjects will first receive SGB with 6 ml normal saline, and after a one-week washout period, this group will receive SGB with 6 ml 1% lidocaine.

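### The nonparametric fallback has no group factor, so an outcome sent to it gets no test of the primary lidocaine-versus-saline difference at T1

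*Protocol article*

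**What the plan says.** The Statistical analyses section of the protocol article first checks distributions: "The normality and homogeneity of all variable distributions will be tested with the Shapiro-Wilk test and Levene’s test, respectively". It then names two inferential routes. The parametric route is: "We will use two-way (2 × 4) ANOVA for inferential statistical analysis of the parametric data, with Tukey’s post hoc tests". The other is: "For nonparametric data, the Friedman test will be used followed by the Wilcoxon post hoc test". No further test is named for outcomes on the second route. The section adds that a statistical analysis plan will be written before the data are analysed.

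Three other places fix what the main comparison is:

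- The Methods part of the abstract says: "T1 is the primary time point for the primary outcome analysis". The Primary outcomes section likewise places the primary outcomes at 15 minutes after the first block.
- Trial design gives group A lidocaine first and saline a week later, and then says: "In contrast, group B will receive the opposite protocol". At T1 the two groups therefore differ by treatment.
- Sample size begins: "With an expected difference of 10 cm/s in peak systolic velocity of the CCA between group means".

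**The concern.** The primary question is whether patients given lidocaine differ at T1 from patients given saline. That is a comparison of two independent, randomised groups. Friedman ranks the repeated values inside each patient and asks whether the conditions differ. Group membership does not enter the statistic. The Wilcoxon test that follows it is naturally read as the signed-rank test, which is also within patients.

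The 2 × 4 ANOVA has a two-level factor, presumably group, so the parametric route can at least carry the randomised comparison. The fallback drops it. A distributional pre-test would then decide whether a primary outcome is tested against saline at all.

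Two things are at stake. A change caused by the injection itself (needle, volume, positioning, time) could be significant and be read as an effect of the block. And the protocol would offer no valid test of the primary hypothesis for that outcome.

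**Working it through.** **1. Which contrast is the trial sized on?** Inputs from Sample size: difference 10 cm/s, SD 10 cm/s, α = 0.05 (two-sided assumed), and the printed β of 0.8 read as power.

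- Normal approximation: n = 2 × (1.96 + 0.84)² × (10/10)² ≈ 15.7, so 16 per group.
- Independent two-sample t-test: 16.71, so 17 per group, which is the protocol's figure. Power at 17 is 80.7%.
- Dropout: 17 / 0.90 = 18.9, so 19 per group and 38 in total, as stated.

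The figure is reproduced as a comparison between two independent groups, which the fallback does not make.

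**2. Does Friedman use the group?** Pooled over both groups, the statistic was the same (0.988) before and after the patients' rows were shuffled. It ignores group labels.

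**3. How likely is the fallback to be used?** There are eight primary measures (four for each of two arteries). If all were truly normal and the checks independent, the chance that at least one fails a 5% normality test is 1 − 0.95⁸ = 34%. The measures are correlated, so this is only an illustration.

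**4. What does the fallback detect?** Simulation with 17 per group, SD 10 cm/s, four time points (T0–T3), normal data and an assumed within-patient correlation of 0.5. The article gives no correlation.

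| Scenario | Test | Rejects |
|---|---|---|
| No drug effect, 5 cm/s response to either injection | Friedman, pooled over groups | about 86% |
| | Wilcoxon T0 vs T1, pooled | about 79% |
| | Rank-sum between groups at T1 | about 5% |
| No drug effect, 5 cm/s period shift | Wilcoxon T1 vs T3 within one sequence | about 45–47% |
| | Rank-sum between groups at T1 | about 5% |
| Drug effect 10 cm/s | Wilcoxon T1 vs T3 within one sequence | about 96% |
| | Rank-sum between groups at T1 | about 77% |
| | t-test between groups at T1 | about 80% |
| | Rank-sum between sequences on (T1−T0)−(T3−T2) | about 97% |

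Over correlations from 0.3 to 0.8, the Friedman figure in the first row ranges from 71% to 100%.

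**5. Would change from baseline do as well?** The SD of T1−T0 is 10 × √(2 × (1 − r)). At r = 0.5 this is 10 cm/s, so power equals that of the T1 test. At r = 0.3 it is 11.8 (less power), and at r = 0.8 it is 6.3 (more power).

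**The case against.** The strongest reply is that this is a crossover. Each patient's T1 and T3 are the two different treatments, so a within-patient test can compare lidocaine with saline. That is right. A reader might infer that the fallback never compares the two treatments, and the documents do not support that. Within one sequence, T1 against T3 has about 96% power at 10 cm/s. If the Friedman conditions were treatment states rather than clock times, which the article does not rule out, the signed-rank test of lidocaine against saline has close to 100% power. What remains is that the within-sequence comparison is confounded with period, and that neither version is the between-group contrast at T1 that the protocol makes primary.

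A reader might also infer that a true drug effect would cancel out. That happens only if both sequences are pooled and T1 is compared with T3 by clock time, a contrast the article does not specify. Nor do the 86% and 79% figures show that the investigators would present a before-after result as the drug effect. They show what the named test responds to.

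A third inference would be that ptosis and flushing ("the rate of ptosis and conjunctival flushing at T1 and T3") must go through Friedman and be summarised as means, given the sentence "All data will be represented by the mean ± standard deviation". The article does not assign them to Friedman. On paired binary data the tie-corrected Friedman statistic coincides with Cochran's Q and uncorrected McNemar (11.27 for all three in a worked example). The test for a binary secondary outcome can be left to the analysis plan, and the article calls these outcomes rates throughout. No finding rests on them.

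Finally, the announced analysis plan might put the matter right. But the problem is not a missing detail: the protocol names a test, and a plan that follows it would inherit the mismatch.

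**Conclusion.** The point holds in this form: the named fallback is a within-patient procedure without a group factor, so it cannot test the randomised difference at T1 that the protocol makes primary and sizes the trial on. That follows from the text and needs no simulation.

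The size does rest on assumptions: normal data, SD 10 cm/s from the protocol, correlation 0.5 (not in the documents), and illustrative 5 cm/s injection and period effects. Under these, a response shared by both injections makes Friedman significant in about 86% of trials and T0–T1 Wilcoxon in about 79%, where a between-group test holds its level near 5%. A within-sequence T1–T3 comparison is falsely positive in about 45–47% under a period shift of that size. The point bears only on outcomes that take the nonparametric route. It should be corrected before analysis.

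**What to change.** In Statistical analyses, replace the Friedman/Wilcoxon sentence for non-normal outcomes with:

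- **Primary comparison:** a Wilcoxon rank-sum (Mann-Whitney) test between the two groups at T1, or on the change T1−T0, with a Hodges-Lehmann estimate and its confidence interval. Choose one of the two before the data are seen.
- **Crossover comparison:** a rank-sum test between sequences on each patient's period difference (T1−T0)−(T3−T2), again with a Hodges-Lehmann estimate. This removes a common period shift and any response shared by both injections.

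Carry the same wording into the statistical analysis plan. The cost is wording only, since all the measurements are already scheduled. With normal data the rank test at T1 gives up a little power against the t-test (about 77% against about 80% at 17 per group and 10 cm/s). The period-difference test has about 97% under the assumed correlation of 0.5.

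### The 2 × 4 ANOVA with Tukey tests has unnamed factors, does not fit the AB/BA crossover, and does not match the single T1 comparison that set the sample size

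*Protocol article*

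**What the plan says.** The protocol article's Statistical analyses section states: "We will use two-way (2 × 4) ANOVA for inferential statistical analysis of the parametric data", with Tukey's procedure as the post hoc step. Non-normal data get a Friedman test followed by Wilcoxon tests. Neither ANOVA factor is named. The section's only two-level term is the pair of groups, whose baseline values are to be described.

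Those groups are treatment sequences. Under Trial design, group A receives lidocaine and then saline. "In contrast, group B will receive the opposite protocol". The Doppler measurements are taken at five times ("as measured at T0, T1, T2, T3, and T4", Data collection process). The Abstract and Primary outcomes make T1, 15 minutes after the first injection, the primary time point.

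The Sample size section rests on one comparison of means: "With an expected difference of 10 cm/s in peak systolic velocity of the CCA between group means", an SD of 10 cm/s, and "α = 0.05, and β = 0.8, a sample size of 17 patients was required in each group". The analysis section also promises a separate statistical analysis plan before analysis.

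**The concern.** In an AB/BA crossover the group label is not the treatment. Each group has one reading after lidocaine and one after saline, so an ANOVA laid out by group and time does not put the treatment comparison where a reader would look for it. The 4 does not match the five measurement times, and the section does not say which time is left out. It also does not say that the ANOVA is a repeated-measures one.

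The Tukey step raises a second problem. The trial was sized for one comparison at α = 0.05. If the declared T1 comparison is instead tested as one of many pairs, it no longer has the power that the sample size was meant to give. At stake are a clear estimate of lidocaine versus saline, the power of the primary comparison and, if pairing is ignored, the error rates.

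**Working it through.** **Inputs.** From Sample size: difference δ = 10 cm/s, SD σ = 10 cm/s, α = 0.05, n = 17 per group (19 enrolled). Assumptions: two-sided testing; the printed β = 0.8 means power 0.80; the SD is that of a single reading between patients. The within-patient correlation ρ is not given; the range 0 to 0.7 is used, equal for all pairs of times.

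**1. The plan's own figure.** For a two-sample t test the non-centrality is δ/(σ√(2/n)) = √(17/2) = 2.915, with 32 df and critical t 2.04. Power is 0.781 at n = 16, 0.807 at 17 and 0.851 at 19. So 17 per group reproduces, as a single unadjusted test. A literal β = 0.8 (power 0.2) would give 3 per group.

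**2. Where the treatment effect sits under group × time (T0–T3).** Take a lidocaine effect d, no saline effect and no carryover.

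| | T0 | T1 | T2 | T3 | Mean |
|---|---|---|---|---|---|
| Group A | 0 | d | 0 | 0 | d/4 |
| Group B | 0 | 0 | 0 | d | d/4 |
| A − B | 0 | +d | 0 | −d | 0 |

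The group difference is 0 for any d. It is also 0 over T1–T4. With a carryover c in group A at T2 and T3, the group difference is (d + 2c − d)/4 = c/2, for example 2.5 cm/s for c = 5. That is carryover, not the lidocaine effect.

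**3. The interaction.** In the repeated-measures form its non-centrality is (n/2)(d² + d²)/(σ²(1 − ρ)). At n = 17, d = 10 and ρ = 0 this is 8.5 × 200/100 = 17. With 3 and 96 df, power is 0.94, and it rises to 0.99 at ρ = 0.3. The effect is detected, but a 3-df test gives no treatment estimate.

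**4. The T1 contrast under Tukey.** The critical t is q(0.95; k, df)/√2, with k the number of means in the family. The non-centrality is √(n/2), as in step 1, and df = 8(n − 1).

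| Family | Critical t (n = 17) | Power, n = 17 | Power, n = 19 |
|---|---|---|---|
| 8 cells (28 pairs) | 4.358/√2 = 3.08 | 0.44 | 0.50 |
| 4 means | 2.60 | 0.62 | 0.69 |
| 2 groups at T1 | 1.98 | 0.82 | 0.86 |

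With the 8-cell family about 31 per group would be needed for 80% power.

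**5. If readings are treated as independent.** The variance of the group mean difference is then understated by the factor 1 + 3ρ. The false-positive rate is about P(|Z| > 1.98/√(1 + 3ρ)), which is 15%, 21% and 26% at ρ = 0.3, 0.5 and 0.7. Simulations of 4,000 trials per setting, at 17 and 19 per group, gave 15–27%. The interaction test is too conservative: its size is about 1% at ρ = 0.3 and lower beyond that.

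**6. What the crossover can deliver.** Comparing T1 − T3 between sequences at 17 per group has power of 0.98 at ρ = 0 and more at higher ρ. The comparison of (T1 − T0) − (T3 − T2) has 0.81, 0.92 and 0.98 at ρ = 0, 0.3 and 0.5. In both, the between-sequence difference estimates 2δ and must be halved.

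**The case against.** The strongest reply is that the layout is inferred. A treatment × time 2 × 4 table can be built: code each reading by the injection given in its period, leave out T4, and all eight cells are filled. Lidocaine then has means (0, δ, 0, δ) and saline (0, 0, 0, 0), so the treatment main effect is δ/2. This would also explain four times rather than five. It stands as a possibility. The section does not state it, and the only two-level term there is the groups.

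A reader might infer that the ANOVA would miss a large lidocaine effect. The documents do not support that. Nothing makes the group main effect the main test, T1 is declared primary, and the interaction test sees the effect. A reader might also take 44% as the trial's power. It is the figure for one Tukey family, and the family is not stated. The error rates in step 5 apply only if pairing is ignored. Friedman and Wilcoxon are within-patient procedures, which suggests that repeated measures may be intended.

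Finally, factor names, error structure and post hoc families are often left to an analysis plan. That disposes of a complaint about missing detail. It does not dispose of this one: the article commits to a particular model and post hoc procedure that fit the design poorly and do not match its own sample-size calculation.

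**Conclusion.** The concern holds in a conditional form. The stated method does not identify the lidocaine–saline comparison. On the most likely reading (group × T0–T3), and without carryover, the group main effect says nothing about it. The interaction detects 10 cm/s with power above 90% but provides no single estimate.

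At 17 per group the Tukey step leaves the T1 contrast with power of 0.44 (8 cells) or 0.62 (4 means), against 0.81 for the test behind the sample size. Only a family confined to the two groups at T1 avoids the loss. If pairing were ignored, the group test would falsely reject about 15–27% of the time for ρ = 0.3–0.7.

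These figures rest on the protocol's 10 cm/s and SD of 10, two-sided α and power 0.80. The correlations are assumed.

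**What to change.** Replace the 2 × 4 ANOVA and the Tukey step with two named analyses.

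- **Primary, as already declared:** one lidocaine-versus-saline comparison at T1, adjusted for T0, at α = 0.05 without Tukey.
- **Crossover analysis:** a linear mixed model on T1 and T3 with treatment, period and sequence as fixed effects, the pre-injection reading (T0 or T2) as covariate and a random patient effect. Report the treatment difference with its 95% CI.

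If the sponsor prefers the crossover estimate as primary, the Abstract and the Primary outcomes section must be changed to say so, because it pools T1 and T3 rather than using T1 alone. Summarise T4 separately, since by then every patient has had both injections.

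The cost is a wording change in the protocol and the analysis plan before the data are analysed, and a little more analysis work. SPSS 21 can fit the mixed model. No new patients or measurements are needed.
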